## Abstract

**Introduction:**

Combination antiretroviral therapy (cART) has massively reduced HIV mortality. However, long-term cART increases the risk of adverse drug reactions (ADRs), which can lead to higher morbidity, mortality and healthcare costs for people living with HIV (PLHIV).

Pharmacovigilance—monitoring the effects of medicines—is essential for understanding real-world drug safety. In Uganda, pharmacovigilance systems have only recently been developed, and rates of ADR reporting for cART are very low. Thus, the safety profile of medicines currently used to treat HIV and tuberculosis in our population is poorly understood.

The Med Safety mobile application has been developed through the European Union’s Innovative Medicines Initiative WEB-Recognising Adverse Drug Reactions project to promote digital pharmacovigilance. This mobile application has been approved for ADR-reporting by Uganda’s National Drug Authority. However, the barriers and facilitators to Med Safety uptake, and its effectiveness in improving pharmacovigilance, are as yet unknown.

**Methods and analysis:**

A pragmatic cluster-randomised controlled trial will be implemented over 30 months at 191 intervention and 191 comparison cART sites to evaluate Med Safety. Using a randomisation sequence generated by the sealed envelope software, we shall randomly assign the 382 prescreened cART sites to the intervention and comparison arms. Each cART site is a cluster that consists of healthcare professionals and PLHIV receiving dolutegravir-based cART and/or isoniazid preventive therapy. Healthcare professionals enrolled in the intervention arm will be trained in the use of mobile-based, paper-based and web-based reporting, while those in the comparison arm will be trained in paper-based and web-based reporting only.

**Ethics and dissemination:**

Ethical approval was given by the School of Biomedical Sciences Research and Ethics Committee at Makerere University (SBS-REC-720), and administrative clearance was obtained from Uganda National Council for Science and Technology (HS1366ES). Study results will be shared with healthcare professionals, policymakers, the public and academia.

**Trial registration number:**

PACTR202009822379650.

Strengths and limitations of this studyThis study will be delivered by researchers, policymakers, software developers, healthcare providers and consumers to promote medication safety in resource-limited settings.We aim to recruit 3820 healthcare professionals from 382 combination antiretroviral therapy sites spread across Uganda; the selected study sites serve 80% of people living with HIV receiving combination antiretroviral therapy.A limitation is that the use of the Med Safety mobile app requires a smartphone, but only 16% of Ugandans own a smartphone; limited rollout showed that 7 in 10 healthcare professionals are smartphone owners.

## Introduction

Spontaneous adverse drug reaction (ADR) reporting is the backbone of pharmacovigilance (PV) globally but is plagued by under-reporting.^1–3^ Only 3% of Ugandan healthcare professionals (HCPs) reported a suspected ADR to the National Pharmacovigilance Centre (NPC) in 2014.^2^ These HCPs cited lack of conventional paper-based ADR forms (paper forms), limited access to web-based forms (web forms) due to the scarcity of internet-wired computers and the lack of feedback to ADR reporters as common barriers to PV. Also, logistical challenges lurk in the countrywide distribution and collection of paper forms by Uganda’s NPC, which hinders timely data collation and analysis.^2^ Ultimately, the implementation of requisite policy actions to safeguard the public from medication-related harm has been delayed.

Innovative interventions are needed to improve ADR reporting, such as the use of mobile applications (mobile apps or apps) to support traditional PV.^4^ Mobile apps have had variable success in PV worldwide. A 10-fold increase in the rate of ADR reporting was seen for a medical device with social media engagement in the USA. In contrast, uptake of mobile app reporting has been poor in Europe: studies in the UK, the Netherlands and Croatia showed 1.7, 1.1 and 6.5 app ADR reports per completed month per 1000 app downloads, respectively.^4 5^ Uptake was also poor in India: 4.0 app ADR reports per completed month per 1000 app downloads.^6^

Efforts to strengthen PV in Uganda are timely due to the recent rollout of dolutegravir (DTG) as the preferred drug for first-line and second-line combination antiretroviral therapy (cART). DTG is more effective and tolerable and has a higher genetic barrier to developing drug resistance than other antiretrovirals.^7^ Rollout began in October 2018 and, by August 2019, over 347 888 people living with HIV (PLHIV) were receiving DTG-based cART.^7^ In addition, Uganda is rapidly scaling up isoniazid preventive therapy (IPT) for the prevention of tuberculosis (TB) in PLHIV. Only 16% of PLHIV had been reached with life-saving IPT by June 2019^8^: an extra 135 711 PLHIV were initiated on IPT by September 2019 after a 100-day scale-up campaign.^7 8^ IPT significantly reduces the incidence of active TB, curbing TB-related mortality among PLHIV.^9^

Although DTG is generally well tolerated, it is associated with serious ADRs including hyperglycaemia,^10–13^ neuropsychiatric effects (1.7%)^14^ and hepatotoxicity (0.1%).^15^ DTG is also associated with more common, but less serious, ADRs such as headache, abnormal dreams and abdominal pain, but the impact of these has not been evaluated in real-world settings in developing countries. The rapid rollout of DTG and scale up of IPT will increase the number of PLHIV exposed to these therapies, potentially increasing the incidence of ADRs, including serious ADRs, associated with these medicines. Discontinuation of DTG and/or IPT is recommended if serious ADRs such as jaundice, blurred vision or hyperglycaemia occur.^16^ Four in 100 000 PLHIV who receive IPT die due to an IPT-related adverse event.^1^

ADRs can reduce quality of life for PLHIV and increase morbidity, mortality and healthcare costs.^17 18^ In 2016, prior to DTG rollout, the NPC attempted to improve spontaneous ADR reporting via a web form. However, they received only 92 online reports versus 290 paper-based ADR reports linked to cART from October 2018 to September 2019. More recently, a PV task force composed of the NPC, the AIDS Control Program and Ministry of Health was set up. The task force established an active drug safety monitoring and management programme to complement the spontaneous ADR reporting system. The NPC received 109 DTG-linked ADR reports from October 2018 to September 2019 from ~348 000 PLHIV. Only 18 IPT-linked ADR reports were received from January 2019 to June 2019 from ~300 000 PLHIV: 2.6 DTG-linked ADR reports per month per 100 000 treated PLHIV and 1.0 IPT-linked ADR report per month per 100 000 treated PLHIV. These rates are barely 5% the known incidence of the ADRs in PLHIV elsewhere.^1 3^

The Med Safety mobile application was developed by the European Union Innovative Medicines Initiative: WEB-Recognising Adverse Drug Reactions. The same technology that produced the Med Safety App was also adopted by European countries including UK’s Medicines and Healthcare products Regulatory Agency (MHRA) in July 2015, Netherlands’ Lareb in January 2016 and Croatia’s HALMED in May 2016. In 2017, the Med Safety App was introduced in Africa (Burkina Faso and Zambia) in partnership with WHO. MHRA adapted Med Safety for low-income and middle-income countries (LMICs) including Uganda with approval from Uganda’s National Drug Authority (NDA) (figure 1).^4^
^,^
19 Med Safety was launched in limited settings in Uganda in February 2020.

**Figure 1 F1:**
[figure not shown]
Med Safety mobile app. MHRA, medicines and healthcare products regulatory agency; NDA, national drug authority.

Med Safety’s platform facilitates easy adoption and low-cost maintenance in LMICs. It is available at no cost for mobile phones and tablets, for Android and iOS, in English. Within the app, ADR reports can be completed offline and transmitted to NPC when internet connectivity is established. The ADR reporting form has a clear and simple format. App users can browse and view ADR data and may create a ‘watch-list’ of *medicines* of their own interest to receive personalised news and alerts. Med Safety provides for two-way exchange of medication safety information between NPC and HCPs. This enhanced interaction promotes the involvement of HCPs in PV activities. The anticipated increase in volume of ADR reports in the national PV database could enhance its signal detection potential^20^ and contribute to remedial efforts to improve patient safety. The app is also integrated into the WHO Collaborating Centre for International Drug Monitoring – Uppsala Monitoring Centre application programme interfaces (including Vigiflow, VigiAccess and WHODrug).^19^ This study seeks to understand whether Med Safety is effective in improving ADR reporting by HCPs if used together with traditional PV methods versus if traditional PV methods are used alone.

### Aims and objectives

Our aim is to assess the feasibility, effectiveness, cost and cost-effectiveness of implementing Med Safety for HCP-driven reporting of ADRs associated with DTG containing cART and IPT for TB prevention in PLHIV in Uganda. Our hypothesis is that the use of Med Safety for ADR reporting by HCPs attending to PLHIV on DTG-based cART and/or IPT will increase the ADR reporting rate^21 22^ by at least 25% versus use of existing PV methods alone in 30 months of follow-up at selected cART sites in Uganda. We will test our hypothesis in a pragmatic multicentre open-label cluster-randomised controlled trial whose specific objectives are to:

Assess the feasibility and acceptability of Med Safety for ADR reporting by HCPs at selected cART sites in Uganda.Determine the app’s effect on the rate of ADR reporting versus traditional PV methods alone.Estimate the app’s cost and cost-effectiveness from the provider perspective.

## Methods and analysis

### Participants, interventions and outcomes

#### Study setting

The study will be conducted nationwide at 382 (of 1832 cART sites) high volume accredited cART sites in Uganda. The 382 cART sites serve 80% of the PLHIV on cART in Uganda.^8^ This protocol follows the Standard Protocol Items: Recommendations for Interventional Trials 2013 statement (online supplemental file 1).^23^

10.1136/bmjopen-2022-061725.supp1Supplementary data

#### Eligibility criteria

All smartphone-owning HCPs at these sites are eligible including: physicians, medical officers, pharmacists, nurses and midwives, clinical officers, pharmacy technicians and community health workers (lay counsellors and expert clients). Limited rollout showed that 7 in 10 HCPs are smartphone owners. Written informed consent will be sought from eligible HCPs. We expect to enrol 10 HCPs per cART site on average.

#### Intervention arm

HCPs at intervention cART-sites will be introduced to the Med Safety mobile app whether they own a smartphone or not. Mobile app, paper form and web form awareness campaigns including initial face-to-face training, posters/brochures and monthly reminder WhatsApp and mobile phone short messages (SMS) for up to 6 months will be undertaken. Training will be conducted by pharmacists from NPC and Makerere University with expertise in PV. The training teams have harmonised the training schedule to ensure uniform training. Interested HCPs with personal smartphones will be invited and assisted to install the mobile app and trained to use it to report suspected ADRs, with emphasis on DTG-linked and IPT-linked ADRs. HCPs will also be trained and encouraged to use traditional PV methods (paper form and web form).

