#### Comparison arm

HCPs at the comparison cART sites will be trained and encouraged to use traditional methods of ADR reporting (paper form and web form). All aspects of the training will be identical to those in the intervention arm except that Med Safety will not be introduced to HCPs in the comparison arm. Reminder WhatsApp and SMS about the paper form and web form will be sent out monthly for up to 6 months.

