#### Outcomes

Our primary outcome is number of HCP-reported ADRs per 100 000 person-months of treated PLHIV per study arm. Our secondary outcomes are number of app ADR reports per 1000 app downloads per month of follow-up; causality (by Naranjo Scale and Liverpool Causality Assessment Tool)^24 25^; seriousness as per the WHO definitions (threatens life, ie, leads to or prolongs hospitalisation, causes incapacitation or death); ADR outcome; cost per ADR report; cost per additional ADR report; and cost per additional avoidable serious ADR report.

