#### Paper form and web form

The paper form and web form details will be distributed at all enrolled cART-sites. PV focal persons based at the cART-sites and NDA regulatory officers will routinely collect the paper forms and forward them to NPC for data capture in the national PV database and central analysis, prior to onward submission to the WHO database, VigiBase. HCPs also have the option to submit online ADR reports using the web form.

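### Printed promotion of paper and web reporting is listed only for intervention sites, so any extra non-app reports it prompts could be credited to the app

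*Protocol article*

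**What the plan says.** The Intervention arm section describes one campaign that covers the app, the paper form and the web form: "Mobile app, paper form and web form awareness campaigns including initial face-to-face training, posters/brochures and monthly reminder WhatsApp" and SMS messages, for up to 6 months.

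The Comparison arm section says that staff will be trained in and encouraged to use paper and web reporting. On parity it says: "All aspects of the training will be identical to those in the intervention arm except that Med Safety will not be introduced to HCPs". It then adds: "Reminder WhatsApp and SMS about the paper form and web form will be sent out monthly for up to 6 months". Posters and brochures are not mentioned.

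Under Data collection, the article says: "The paper form and web form details will be distributed at all enrolled cART-sites". The end of the Introduction asks if the app would be "effective in improving ADR reporting by HCPs if used together with traditional PV methods versus if traditional PV methods are used alone". The primary outcome (Outcomes) is a rate of ADRs reported by healthcare professionals (HCPs), with no restriction by channel. The only channel-specific outcome is secondary: "Our secondary outcomes are number of app ADR reports per 1000 app downloads per month of follow-up".

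**The concern.** The trial is meant to isolate what the app adds to the same traditional methods. The article describes both arms component by component, and the two lists differ by one item that is not the app. That item promotes paper and web reporting as well as the app.

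If the materials go only to intervention sites, they may prompt paper or web reports that comparison sites had no equal prompt to make. The primary outcome would count those reports, and the Effectiveness section would read the arm difference as the app's effect. Randomisation does not help, because the difference arises after allocation. App reports per 1000 downloads cannot reveal it either, because that measure ignores paper and web reports.

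The economic result is also touched. Brochures are a listed running cost (Economic cost data), so which arm receives them affects the incremental cost as well as the report count.

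**Working it through.** **1. Components side by side**

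| Component | Intervention arm | Comparison arm |
|---|---|---|
| Face-to-face training | Listed | Stated to be identical apart from the app |
| Monthly WhatsApp/SMS reminders, up to 6 months | Listed | Listed |
| Posters/brochures | Listed | Not mentioned |
| Paper form and web form details | All sites | All sites |
| Med Safety | Introduced | Not introduced |

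The parity sentence is limited to training. The Comparison arm section states reminders separately, so it does not treat training as covering the whole campaign. Of the two non-training components, one is carried over and the other is not. The form details sent to all sites put the reporting tools in place, but that sentence does not mention posters or brochures.

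**2. The plan's own figure**

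The Sample size section gives mean 1.0, SD 1.179, effect 25% (difference 0.25), power 80%, 95% confidence (taken as two-sided 5%), 10 HCPs per site and a coefficient of variation of 0.25.

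- Individuals per arm: 2 × (1.960 + 0.842)² × 1.179² / 0.25² = 349.1, so 350.
- Sites per arm: 350 × [1 + (10 − 1) × 0.25] / 10 = 350 × 3.25 / 10 = 113.75, so 114. This matches the plan, but uses 0.25 as an intracluster correlation.
- With 0.25 as a between-cluster coefficient of variation: 1 + 7.849 × [2 × 1.179²/10 + 0.25² × (1² + 1.25²)] / 0.25² = 56.03, so 57 per arm.

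The present point does not depend on which reading is right, so both are carried forward.

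**3. Illustration under an assumption**

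The documents give no effect for posters or brochures. Assume that the app has no effect and displaces no paper or web reports, and that the printed materials raise reporting in the intervention arm by a fraction x. There are 191 sites per arm.

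- SE, 0.25 as intracluster correlation: √[2 × 1.179² × 3.25 / (191 × 10)] = 0.0688.
- SE, 0.25 as coefficient of variation: √{[2 × 1.179²/10 + 0.25² × (1 + (1 + x)²)] / 191} = 0.0463, 0.0467 and 0.0471 for x = 0.05, 0.10 and 0.15.
- Chance of two-sided p<0.05: Φ(x/SE − 1.96) + Φ(−x/SE − 1.96).

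| Assumed x | x as share of the 25% target | Chance, intracluster correlation | Chance, coefficient of variation |
|---|---|---|---|
| 0 | 0 | 5% | 5% |
| 5% | 5/25 = 20% | 11% | 19% |
| 10% | 10/25 = 40% | 31% | 57% |
| 15% | 15/25 = 60% | 59% | 89% |

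The table shows only that an imbalance, if there is one, passes straight into the primary comparison. It does not show that one exists.

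**The case against.** The strongest reply is that this is silence in a condensed article. Nothing says that comparison sites receive no posters or brochures, and the Comparison arm section is not presented as a closed list. Several sections suggest that only the app was meant to differ:

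- The abstract separates the arms by mobile-based reporting alone.
- Paper and web form details go to all sites.
- Cost and cost-effectiveness provides for setup and running costs in both strategies, and brochures are a running cost.
- Dissemination strategies speaks of communication tailored to each arm.

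Two of the three campaign components are matched in any case. A rise in paper or web reports caused by introducing the app itself would be a legitimate part of its effect.

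Most of this stands. It shows that parity was probably intended and that unequal delivery is not proven. But none of these sections gives comparison sites the printed materials, and a team following the two arm descriptions would deliver them to one arm only.

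A reader might infer that the arms will certainly be unequal, that intervention sites get continuous on-site promotion, or that most of the 25% target could be spurious. The documents support none of these. They do not say how long posters stay up or what each one promotes, and any size rests on an assumed uplift. Reminders are not part of the problem, because both arms have them monthly for up to 6 months.

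**Conclusion.** The point holds as a conditional weakness in how the contrast is specified. As written, printed promotion of paper and web reporting is listed for one arm only. If it is delivered that way, the trial compares the app plus printed promotion with neither, and part of any difference in the all-channel primary rate could be wrongly credited to the app.

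The size cannot be established from the documents. The 5% to 15% uplifts are assumptions. They also presume no app effect and no displacement of paper or web reports, and they use the plan's own variance inputs. The case for acting rests on the mismatch between the two arm descriptions and on the low cost of removing it.

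**What to change.** Amend the Comparison arm section so that comparison sites receive the same posters and brochures with app content removed, on the same schedule as intervention sites.

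The Sample size section reports 629 HCPs at 87 sites from limited rollout, so some comparison sites are probably already enrolled; the split by arm is not given. First establish what they received. If they did not receive the materials, supply them, record the date at each site and disclose the difference, since this adds promotion part-way through follow-up. If matching is not done, describe the tested intervention as the app plus its printed promotion wherever the effect is stated.

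Report the primary rate by channel and arm as supporting description only. It cannot settle the question: the app may displace paper and web reports, or legitimately raise them.

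The cost is printing for up to 191 comparison sites, delivered at the training visit where that is still to come and separately where it is not, plus one table. The downside is a small print cost and possibly a smaller observed effect.

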#### Comparison arm

HCPs at the comparison cART sites will be trained and encouraged to use traditional methods of ADR reporting (paper form and web form). All aspects of the training will be identical to those in the intervention arm except that Med Safety will not be introduced to HCPs in the comparison arm. Reminder WhatsApp and SMS about the paper form and web form will be sent out monthly for up to 6 months.

#### Outcomes

Our primary outcome is number of HCP-reported ADRs per 100 000 person-months of treated PLHIV per study arm. Our secondary outcomes are number of app ADR reports per 1000 app downloads per month of follow-up; causality (by Naranjo Scale and Liverpool Causality Assessment Tool)^24 25^; seriousness as per the WHO definitions (threatens life, ie, leads to or prolongs hospitalisation, causes incapacitation or death); ADR outcome; cost per ADR report; cost per additional ADR report; and cost per additional avoidable serious ADR report.

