#### Sample size

To estimate the number of cART sites required per arm for an effect size of 25%,^26^ we assume power of 80% at the 95% confidence level, mean of 1.0 IPT-linked ADR/month/100 000 treated PLHIV (0.00001) and SD of 1.179 IPT-linked ADRs/month/100 000 treated PLHIV (0.00001179) (SD was computed based on the monthly IPT-linked ADR reports submitted to NPC for 1 year from October 2018 to September 2019), cluster size of 10 HCPs and coefficient of variation of 0.25,^26^ which yields ~114 cART sites per trial arm or 228 in both study arms. A minimum of 189 cART sites per arm or 378 in both study arms (66% increment) will be required to cater for the following limitations: (1) the large proportion of HCPs who do not own smartphones of ~50%–60% as previously estimated^21 22^ – and is 26% (95% CI of 23% to 30%) from limited rollout of RCT; (2) refusal to participate by eligible HCPs of ~5% as previously estimated^27^ – and is 0% (95% CI of 0% to 2%) from limited rollout of RCT; (3) loss to follow-up due to the relatively long follow-up period of 30 months (~10%); and (4) contamination due to information sharing between study arms through social media (~30%).^28^ We shall enrol 382 cART sites (191 per study arm) to cater for other unforeseen limitations; thus, recruiting up to 3820 HCPs (1910 HCPs per trial arm). Limited rollout of the RCT suggests a cluster size of 7.2 (629/87) HCPs. We shall retain the average cluster size of 10 HCPs because the RCT has not yet enrolled from the central region of Uganda (with the country’s capital city) where cART sites tend to be much larger with more HCPs per site than the more rural eastern, western and northern regions.

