#### Effectiveness

Descriptive data will be aggregated to obtain the number of HCP-reported ADRs per 100 000 treated PLHIV per trial arm and compared at cluster level using the Student’s t-test or Wilcoxon rank-sum test, as appropriate, to determine if the app significantly increases ADR reporting. We will assess if the introduction of Med Safety increases the rate of ADR reporting by HCPs to NPC versus the use of existing PV methods (paper and online) alone during 30 months of follow-up and effect size of 25% at 5% level of statistical significance and power of 80%.

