#### Cost and cost-effectiveness

We will estimate unit *setup* and *running costs* for both the introduction of Med Safety in addition to existing PV methods and the use of existing PV methods alone. Costs per ADR report submitted to NPC will be computed (overall; per study arm; per ADR attribute, eg, seriousness, avoidability, causality, etc). We will estimate cost-effectiveness of introducing Med Safety by calculating the incremental cost-effectiveness ratio, which is the cost per additional ADR report submitted to NPC.

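### The secondary outcome of cost per additional avoidable serious ADR report has a denominator likely to be near zero at the protocol's own report volumes, so it should not stand as a bare ratio

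*Protocol article*

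**What the plan says.** The Outcomes section of the protocol article ends its list of secondary outcomes with three cost measures, the last being "cost per additional avoidable serious ADR report". The Cost and cost-effectiveness section describes one incremental ratio only: "calculating the incremental cost-effectiveness ratio, which is the cost per additional ADR report submitted to NPC". There, seriousness and avoidability appear as report attributes by which an average cost per report will be broken down.

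The protocol also gives what is needed to project total report volume. The Introduction states that "The NPC received 109 DTG-linked ADR reports from October 2018 to September 2019", from about 348 000 treated people, and that "Only 18 IPT-linked ADR reports were received from January 2019 to June 2019", from about 300 000. It converts these to "2.6 DTG-linked ADR reports per month per" 100 000 treated people, and 1.0 for isoniazid preventive therapy (IPT). Aims and objectives sets the target as a rise in the reporting rate "by at least 25% versus use of existing PV methods alone in 30 months of follow-up". Study setting says that the 382 sites serve 80% of people on cART, and they are split 191 to 191.

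The article states no serious share, no avoidable share and no expected number of reports that are both.

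**The concern.** An incremental ratio behaves acceptably only when its denominator is well away from zero relative to its sampling error. Here the denominator is the difference between arms in a subset of an already small number of reports. If that difference is about as large as its standard error or smaller, the ratio can be very large, undefined or negative by chance, and a conventional confidence interval for it has no useful meaning.

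Objective 3 concerns cost and cost-effectiveness, and the protocol expects policymakers and regulators to use the results at once. A single figure would be read as the price of one more avoidable serious reaction reported. At the planned volumes, chance could determine most of its value.

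**Working it through.** **Step 1. Reproduce the protocol's baseline rates (Introduction).**
- Dolutegravir (DTG): 109 / 12 months / 3.48 (hundred thousands) = 2.61 per month per 100 000. Stated: 2.6.
- IPT: 18 / 6 / 3.00 = 1.00. Stated: 1.0.

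Both agree.

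**Step 2. Project reports per arm.** Formula: treated people × 0.80 / 2 × monthly rate × 30. This assumes that national rates and 2018–19 patient numbers hold at the trial sites, that the 80% coverage applies to both treatments, and that patients divide equally between arms.
- DTG: 348 000 × 0.40 = 139 200; × 2.61 per 100 000 × 30 = 109.
- IPT: 300 000 × 0.40 = 120 000; × 1.0 per 100 000 × 30 = 36.
- Comparison arm: 109 + 36 = 145.
- Intervention arm at +25%: 145 × 1.25 = 181.
- Extra reports of any kind: about 36.

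**Step 3. Take the serious-and-avoidable subset.** The share is not in the protocol, so 2%, 9% and 25% are assumptions. The same 25% effect is applied to the subset. With independent Poisson counts of means m0 and m1, the standard error of the difference is √(m0 + m1). The chance of a difference of zero or less comes from the exact distribution of the difference between two Poisson counts (Skellam).

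| Assumed share | m0 | m1 | Expected difference | SE | P(difference ≤ 0) |
|---|---|---|---|---|---|
| 2% | 2.9 | 3.6 | 0.7 | 2.5 | 47% |
| 9% | 13.1 | 16.3 | 3.3 | 5.4 | 31% |
| 25% | 36.3 | 45.3 | 9.1 | 9.0 | 17% |
| 100% (all reports) | 145 | 181 | 36 | 18 | 2.4% |

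The last row shows that the ratio per additional report of any kind is much less exposed.

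**Step 4. Check against clustering.** A simulation of 382 sites with a between-site coefficient of variation of 0.25 and unequal site sizes, for shares of 3% to 25%, gave a zero or negative difference in 43% to 20% of trials on counts and 36% to 16% on rates. The Poisson answer for those shares is 43% to 17%, so the conclusion does not depend on ignoring clusters.

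**Step 5. Vary the volume.**
- All cART-linked reports plus IPT: the Introduction gives 92 + 290 = 382 cART-linked reports in a year. 382 / 12 × 0.40 × 30 = 382, plus 36 for IPT, gives 418 in the comparison arm and 104.5 extra. Shares of 3% to 25% give about 3 to 26 extra reports and a 31% to 5% chance of a difference of zero or less.
- Reporting five times the baseline in both arms: 29%, 10% or 1% for shares of 2%, 9% or 25%.
- To bring the chance below 2.5%, about 142 avoidable serious reports are needed in the comparison arm. That is about 4 times the projected count at a 25% share (142 / 36) and about 10 times at a 10% share (142 / 14.5).

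**The case against.** The strongest reply is that the protocol fixes only the 36 extra reports. The range of about 1 to 9 depends on a share that it never states. That is correct, and the range should be quoted only as conditional on the assumed 2% to 25%.

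The second reply is that 2018–19 volume is a floor. DTG and IPT were being scaled up, the Introduction puts reporting at about 5% of known incidence, and both arms receive training and reminders. This also stands: step 5 shows the problem shrinking and, with five-fold reporting and a 25% share, almost vanishing. It does not vanish at the lower shares. The contamination of about 30% that the Sample size section allows for would push the other way.

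Three stronger readings are tempting, but the protocol does not support them.
- *Much larger overdispersion.* A reader might take the monthly SD in the Sample size section (1.179 on a mean of 1.0) and infer a variance about 4.2 times Poisson: (1.179 × 3)² / 3. That SD describes month-to-month variation in national IPT reports. Variation shared by both arms largely cancels in their difference, and the ratio does not carry over to a small subset. Under independent thinning it becomes 1 + share × 3.2, or about 1.3 at 9% and 1.8 at 25%. A normal approximation then gives about 30% and 23%, against 38% and 31% with 4.2 applied unchanged.
- *A negative ratio cannot be interpreted.* The intervention adds the app and its costs to otherwise identical training, so incremental cost is very likely positive. A negative value would then mostly mean higher cost and fewer reports. What remains unreliable is the size of the ratio.
- *Avoidability has no assessment method.* The article names no tool, but it may leave this to the full protocol. It is no contradiction.

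Finally, this is the last-listed secondary outcome, and the main ratio is already per report of any kind. That limits the consequence, but it does not make the listed outcome estimable.

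**Conclusion.** The point holds in a limited form. The protocol's own figures imply about 36 extra reports of any kind, so a serious-and-avoidable subset is likely to give a difference at or below about one standard error. With assumed shares of 2%, 9% or 25%, the denominator is zero or negative in about 47%, 31% or 17% of trials even if the 25% effect is real.

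This rests on the unstated share, on Poisson counts, on 2018–19 rates and patient numbers persisting, and on the same 25% effect in the subset. It is a weakness in how one secondary outcome is expressed. It does not show that the cost-effectiveness analysis as a whole fails, because the ratio per additional report of any kind has only about a 2.4% chance of a non-positive denominator on the same assumptions.

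**What to change.** In the Outcomes and the Cost and cost-effectiveness sections, express this outcome as two figures side by side: the between-arm difference in avoidable serious reports per 100 000 person-months with a 95% CI, and the incremental cost. Show their joint uncertainty by resampling sites within arm, as a cost-effectiveness plane or as net benefit over a range of values per report. Keep cost per additional ADR report of any kind as the headline ratio.

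If a ratio for avoidable serious reports is also given, show it only with that uncertainty. It should not be withheld by a rule tied to whether the interval includes zero, because reporting of a prespecified outcome would then depend on statistical significance.

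The cost is a change of wording and a little more analysis, with no change to sites, follow-up or recruitment. The downside is that readers get no single headline cost per avoidable serious report.
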